### Participant timeline {13}

Table 2 shows the chronogram of study activities including intervention implementation schedule across study groups and the corresponding measurements of ECD and nutritional status outcomes among pregnant women and children. The number of repeated measurements across time will depend on the timing when each group starts being exposed to the intervention.

**Table 2 Tab2:** Chronogram of study activities and measurements of child development scales

Activities	Study calendar period						
	t0	t1	t2	t3	t4	t5	t6
Community’s allocation	X						
Eligibility in communities A		X					
Enrollment in communities A		X					
Measurement in communities A*		X	X	X	X	X	X
Eligibility in communities B			X				
Enrollment in communities B			X				
Measurement in communities B*			X	X	X	X	X
Eligibility in communities C					X		
Enrollment in communities C					X		
Measurement in communities C*					X	X	X
Eligibility in communities D							X
Measurement in communities D							X
Measurement of CDE-II		X	X	X	X	X	X
Measurement of MSCA							X
Measurement of BSID-III		X	X	X			
Nutritional status assessment		X	X	X	X	X	X

*Intervention starts right after their first measurement. There will be a time span of 6 months between the mid-point of consecutive periods and an approximate time span of 6 months between consecutive individual measurements

### Sample size {14}

Our main outcome statistic is the proportion of children with developmental lag (yellow category) or at risk of development delay (red category). The effect will be assessed comparing these proportions between the exposed groups and the unexposed group.

Sample sizes were planned so that there are approximately 150 children for each 6-month age interval; this approximates a uniform distribution of observations across age groups and study groups for the relevant age ranges. As mentioned before, given the stepped-wedge design of the study, groups will be incorporated sequentially but comparisons between study groups will be performed at the same study calendar period and for children at the same age interval (see Table 1 for a representation of the stepped-wedge design). Group A will include 1–30-month-old children (*n* = 750); these children will be 31–60 months old at their final measurement and compared to children with the same ages in group D (*n* = 750). This will allow to assess the effect of NPECDP-UKA on ECD after an exposure time of 30 months. Other comparisons are possible. For example, ECD outcomes from group B vs group D (*n* = 900) and group C vs group D (*n* = 1200) at the final study calendar period (Table 1). Table 3 shows the effect size in terms of a difference of proportions given different levels of proportions in the unexposed group (group D), different design effects (DEFF) that consider that measurements in the same community are correlated (DEFF = 1.5, 2.0) [31], a significance level of 0.05 under a bilateral test, and a statistical power of 80.0%.

**Table 3 Tab3:** Sample sizes and effect sizes in terms of a difference of proportions between two groups given a statistical power of 80%

Sample size per group	Proportion in the group without exposure to NPECDP-UKA	Effect size (difference of proportions) given different design effects (DEFF)*		
		DEFF = 1.0	DEFF = 1.5	DEFF = 2.0
750	0.50	0.072	0.088	0.102
900	0.50	0.066	0.081	0.093
1200	0.50	0.057	0.070	0.081
750	0.25	0.065	0.080	0.093
900	0.25	0.059	0.073	0.085
1200	0.25	0.051	0.063	0.073
750	0.125	0.052	0.064	0.075
900	0.125	0.047	0.058	0.068
1200	0.125	0.040	0.050	0.058

*The design effect is a factor that when multiplied by the variance of an estimator under a simple random sampling design corresponds to its variance under a complex sampling design; in this case, a design with clustering of observations within communities

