**Methods:**

We will use a cluster randomized stepped-wedge design with an allocation ratio of 1:1. Communities will be randomly assigned to each study group: four groups of twenty communities each. We expect that children from intervened communities will show better ECD outcomes.

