#### Plans to promote participant retention and complete follow-up

To promote participant retention, a community commissioner will be identified in each community. These commissioners will be women who support the NPECDP-UKA implementation as translators and interpreters. They will contact the study participants during the intervention, motivating them to attend all workshops and the data collection during the whole duration of the study.

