#### Methods in analysis to handle protocol non-adherence and any statistical methods to handle missing data

Complete case analysis will be performed as well as multiple imputation analysis when appropriate [39]. In regard to adherence, analyses will be complemented with a dose-response analysis.

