## Trial status

Recruitment started in July 2019 and was scheduled to end in June 2022. During the first year of the study, once potential participants had been identified, researchers conducted two recruitment phases: the first one from July 15 to December 19, 2019, and the second one from January 21 to February 10, 2020. Due to the COVID-19 public health emergency, recruitment was suspended during early March 2020. Baseline measurements were obtained for a total of 1176 children (764 whose caregivers decided to enroll and 412 whose caregivers decided not to enroll in the NPECDP-UKA).

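### Table 3 uses the entry numbers of the closed cohorts as their analysed numbers at t6, with no allowance for loss, while group D cannot lose anyone to follow-up

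*Protocol article*

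**What the plan says.** The planning rule is stated under Sample size: "Sample sizes were planned so that there are approximately 150 children for each 6-month age interval". Five such bands give 750. The section applies that number to group A at entry ("Group A will include 1–30-month-old children", n = 750) and again at the end, where "these children will be 31–60 months old at their final measurement and compared to children with the same ages in group D", also 750. Groups B and C are compared with D at the last calendar period with 900 and 1200, which are six and eight bands. Table 3 gives detectable differences for 750, 900 and 1200 per group, using "a significance level of 0.05 under a bilateral test, and a statistical power of 80.0" percent.

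Table 2 shows one enrolment point per group: t1 for A, t2 for B and t4 for C. It shows no later replenishment. The Design and setting section says group D is measured once, and Table 2 puts that measurement at t6.

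The article plans for drop-out elsewhere. It has a retention measure ("To promote participant retention, a community commissioner will be identified in each community"), and the missing-data section says "Complete case analysis will be performed as well as multiple imputation analysis when appropriate". Trial status reports baseline measurements on 1176 children: "764 whose caregivers decided to enroll and 412 whose caregivers decided not to enroll in the NPECDP-UKA". No attrition rate and no inflation factor appear anywhere.

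**The concern.** A number recruited at 1–30 months of age is treated as the number analysed 30 months later. Two things depend on it.

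- **Precision.** The detectable differences in Table 3 are those of a cohort that loses nobody. Any loss in A, B or C moves the real design away from the stated 80%.
- **Comparability.** Follow-up loss can occur only in A, B and C, because D's single measurement takes place when its children enter. At t6 a complete-case comparison therefore sets families who enrolled and stayed against families who have just been recruited. The Discussion says the experimental component avoids self-selection bias because everyone in it has chosen the programme. That reasoning covers selection at entry, not selection by staying.

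**Working it through.** **1. Reproduce Table 3.** Inputs from Sample size: two-sided 0.05, 80% power, equal groups, control proportion p, design effect DEFF. I used the pooled-variance test of two proportions with effective size n/DEFF per group and solved for the difference. At n = 750 and p = 0.50 this gives 0.0721 / 0.0881 / 0.1016 for DEFF 1.0 / 1.5 / 2.0, against the printed 0.072 / 0.088 / 0.102. All 27 cells agree to within about 0.0005, provided the exposed proportion is taken as control plus the difference. Every cell uses the full 750, 900 or 1200, so the table contains no loss factor.

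**2. Margin in the reported enrolment.** If all 764 enrolled children belong to group A: (764 − 750)/764 = 14/764 = 1.8%.

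**3. Power with loss in A only.** The article gives no loss rate, so 10%, 20% and 30% are assumptions. D stays at 750, p = 0.50, DEFF = 1.5, true difference 0.088.

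Example at 20% loss:
- n_A = 764 × 0.80 = 611; effective sizes are 750/1.5 = 500 and 611/1.5 = 407.3.
- Pooled proportion = (500 × 0.500 + 407.3 × 0.412)/907.3 = 0.4605.
- Null SE = √[0.4605 × 0.5395 × (1/500 + 1/407.3)] = 0.03327.
- Alternative SE = √[0.25/500 + 0.412 × 0.588/407.3] = 0.03309.
- Power = Φ[(0.088 − 1.96 × 0.03327)/0.03309] = Φ(0.689) = 75.5%.

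For the alternative in which A's design effect falls with cluster size, DEFF 1.5 at 750/20 = 37.5 children per community implies an intracluster correlation of 0.5/36.5 = 0.0137. At 20% loss A's DEFF is then 1 + (30.55 − 1) × 0.0137 = 1.405.

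| Assumed loss in A | A at t6 | Power at 0.088, DEFF 1.5 | Power, A's DEFF recalculated | Detectable difference, DEFF 1.5 | Enrolment needed for 750, 750/(1 − loss) |
|---|---|---|---|---|---|
| 10% | 688 | 78.1% | 78.7% | 0.090 | 834 |
| 20% | 611 | 75.5% | 76.9% | 0.093 | 938 |
| 30% | 535 | 72.2% | 74.8% | 0.097 | 1072 |

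**4. The other rows.** The hypothesis is better development, so the exposed proportion should be lower than control. For a reduction with 750 per group, the detectable differences are 0.060 / 0.073 / 0.083 at p = 0.25 and 0.044 / 0.053 / 0.060 at p = 0.125. All are smaller than printed (0.065 / 0.080 / 0.093 and 0.052 / 0.064 / 0.075). Power at the printed differences, DEFF 1.0 / 1.5 / 2.0:

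| Loss in A | p = 0.25 | p = 0.125 |
|---|---|---|
| 20% | 82 / 84 / 85% | 89 / 91 / 93% |
| 30% | 79 / 81 / 82% | 87 / 89 / 91% |

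**5. Bias, as an illustration only.** If a fraction f of A is lost and the lost children's prevalence differs from that of the retained by d, the complete-case rate in A is off by f × d. With f = 20% and d = 10 points (both assumed) that is 2 points, against a detectable difference of 8.8. The sign follows the sign of d, which is unknown.

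**The case against.** The power cost is moderate even in the worst row. Table 3 is a grid that already runs from 0.072 to 0.102 across design effects at p = 0.50, and the band size is described as approximate. A reader might infer that the stated numbers and 80% power cannot be reached. The documents do not support that: loss rates are not given, and six of the nine n = 750 cells stay above 80% at 20% loss if the effect is a reduction. What stands is that the p = 0.50 rows have no slack, and the article does not say which control proportion is expected.

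A reader might also take the 1.8% margin as fact. Trial status does not assign the 764 to group A. The link rests on the first-year timing and on decliners being measured only in A. If some of the 764 belong elsewhere, the margin is smaller. Recruitment was also suspended, and the article does not say whether it was complete for that group.

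On bias, multiple imputation is already planned alongside complete cases, so the plan is not complete-case only, and imputation detail may sit in an analysis plan not shown. The remaining gap is that the article does not say which analysis carries the A–C versus D comparisons. It is tempting to add that D contains recent arrivals and should be restricted to long-standing residents. No section gives any migration figure, and the restriction would be only a partial remedy: it cannot identify D families who left, or who would have dropped out of a programme they had not yet started.

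**Conclusion.** The point holds as a matter of planning and labelling. For A the entry number is explicitly carried to t6. For B and C the same band rule and single enrolment point apply, again without an allowance. At p = 0.50 the printed detectable differences hold only with almost no loss: 1.8% if the 764 are group A. Under assumed losses of 10–30% in A at DEFF 1.5, power is roughly 72–79% and the detectable difference rises from 0.088 to as much as 0.097. At lower control proportions, a reduction leaves enough slack to absorb 20% loss.

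The one-sided loss matters more than the power, because recruiting more children would not remove it. Its direction and size cannot be known from the documents, so it qualifies the Discussion's statement on self-selection without refuting it. This should be corrected, but it does not invalidate the design.

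**What to change.** 1. Restate Table 3 with the numbers expected at t6 in A, B and C, unequal against D, under 10%, 20% and 30% loss. From the planned numbers these are 675 / 600 / 525 for A, 810 / 720 / 630 for B and 1080 / 960 / 840 for C; A can instead start from 764 if that figure is confirmed as group A. Compute the 0.25 and 0.125 rows for a reduction.
2. Name as the main t6 analysis the one that corrects for loss in A–C, by imputation or retention weights using t1 covariates (entry covariates for B and C) and earlier CDE-II results, which are already collected. Keep complete cases as sensitivity.
3. Qualify the Discussion's self-selection statement as applying at entry.
4. Optionally, use length of residence in D in a sensitivity analysis, not to restrict the main comparison.

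The cost is a revised table, a few sentences, some extra analysis work and, at p = 0.50, slightly less favourable stated detectable differences. Item 4 needs one residence question in D if it is not already asked.

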This paper aims to present the impact evaluation protocol to assess the effect of the NPECDP-UKA on ECD in preschool children from eighty high social deprived communities in Oaxaca, Mexico. The evaluation has the potential to visualize the effects of an educational intervention performed by an NGO on ECD. It represents an opportunity to assess the developmental lag in the studied communities as well as to provide elements for the continuation, expansion, or modification of the interventions. As part of the civil society and in coordination with authorities, UKA provides a channel to deliver ECD parenting education focused on responsive caregiving. Given the multiple aspects of nurturing care, it is important to have in place multisectoral interventions [19]. Along with the important role from the government, the private sector as well as the civil society can add coordinated contributions to improve and sustain ECD interventions.

The present protocol shows a novel way to assess the effects of an intervention on developmental outcomes where difference scores are not possible due to the age-specific nature of developmental scales. The proposed stepped-wedge experimental design overcome this difficulty and tackle different sources of biases from self-selection, cohort, and community effects. Additionally, the quasi-experimental component of the evaluation allows to study determinants of participation and controls for community and cohort effects. The design could be adapted and applied for studying any other outcome for which age-specific scales are used. Furthermore, it provides useful elements for designing future evaluations by making explicit important biases that may be at play.

To the best of our knowledge, this evaluation study and its design is the first effort of its kind applied to ECD outcomes in Mexico. We hypothesized that children from intervened communities will show better ECD outcomes.

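### Table 3: the rows for control proportions 0.25 and 0.125 give detectable increases in developmental lag, not the reductions the trial hopes to show

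*Protocol article*

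**What the plan says.** The Sample size section of the protocol article defines the quantity being powered: "Our main outcome statistic is the proportion of children with developmental lag (yellow category) or at risk of development delay (red category"). The effect is the comparison of these proportions between exposed groups and the unexposed group.

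The section then introduces the detectable differences: "Table 3 shows the effect size in terms of a difference of proportions given different levels of proportions in the unexposed group (group D"). The levels are 0.50, 0.25 and 0.125, at "a significance level of 0.05 under a bilateral test, and a statistical power of 80.0"%. The sizes per group are 750 ("Group A will include 1–30-month-old children (*n* = 750"), compared with group D), and 900 and 1200 for the other two comparisons ("group B vs group D (*n* = 900) and group C vs group D (*n* = 1200")). The columns are design effects of 1.0, 1.5 and 2.0.

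The differences are printed without a sign, and neither the heading nor the footnote says whether the exposed proportion lies above or below the control proportion. The Background section supplies the expected direction: "We hypothesized that children from intervened communities will show better ECD outcomes".

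**The concern.** Yellow or red is an adverse result, so a better outcome means a smaller proportion in the exposed group. The detectable effect of interest is therefore exposed proportion = control proportion minus d.

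Away from 0.50 the direction matters, because the binomial variance p(1 − p) depends on where the exposed proportion falls. Below 0.50 a move upwards raises the variance and a move downwards lowers it, so the smallest detectable increase is larger than the smallest detectable decrease. If the table was solved for an increase, its entries at 0.25 and 0.125 do not answer the question the trial asks.

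What is at stake is the accuracy of the article's only statement of power. It covers the 30-month comparison (A vs D) and both of the others.

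**Working it through.** **Inputs** (Sample size section and Table 3): two-sided α = 0.05, z = 1.960; power 80%, z = 0.842; equal groups of n = 750, 900 or 1200; control proportion p₁ = 0.50, 0.25 or 0.125; design effect (DEFF) 1.0, 1.5 or 2.0. Table 3's footnote defines the design effect as a multiplier of the variance, so the effective size is m = n/DEFF.

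**Formula.** Solve for d in

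d = 1.960·√(2·p̄·(1 − p̄)/m) + 0.842·√((p₁(1 − p₁) + p₂(1 − p₂))/m), with p̄ = (p₁ + p₂)/2,

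once with p₂ = p₁ + d and once with p₂ = p₁ − d.

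**One cell in full: n = 750, p₁ = 0.125, DEFF 2.0, so m = 375; the table prints 0.075.**

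- Increase: p₂ = 0.2004, p̄ = 0.1627. First term 1.960·√(0.27246/375) = 0.0528; second term 0.842·√(0.26961/375) = 0.0226; sum 0.0754. This is the printed value.
- Decrease: p₂ = 0.0651, p̄ = 0.09505. First term 1.960·√(0.17203/375) = 0.0420; second term 0.842·√(0.17024/375) = 0.0179; sum 0.0599.

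**All 27 cells.** With p₂ = p₁ + d, every printed entry is reproduced to three decimals. With p₂ = p₁ − d, the nine entries at 0.50 are reproduced (they are symmetric) and none of the other 18 is. The choice of formula does not explain this. The unpooled version moves no solution by more than 0.0004, and no downward solution (unpooled or continuity-corrected) gives the printed rows at 0.25 and 0.125. Nor does holding the variance at the control proportion.

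**Printed entries against detectable reductions (DEFF 1.0 / 1.5 / 2.0)**

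| Control proportion | n per group | Printed | Reduction at 80% power | Power if the printed value is a reduction |
|---|---|---|---|---|
| 0.25 | 750 | 0.065 / 0.080 / 0.093 | 0.060 / 0.073 / 0.083 | 86% / 88% / 89% |
| 0.25 | 900 | 0.059 / 0.073 / 0.085 | 0.055 / 0.067 / 0.076 | 86% / 87% / 88% |
| 0.25 | 1200 | 0.051 / 0.063 / 0.073 | 0.048 / 0.058 / 0.067 | 85% / 86% / 87% |
| 0.125 | 750 | 0.052 / 0.064 / 0.075 | 0.044 / 0.053 / 0.060 | 92% / 94% / 95% |
| 0.125 | 900 | 0.047 / 0.058 / 0.068 | 0.040 / 0.049 / 0.055 | 91% / 93% / 94% |
| 0.125 | 1200 | 0.040 / 0.050 / 0.058 | 0.035 / 0.043 / 0.049 | 89% / 92% / 93% |

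Taken as increases, the same printed values have 79.5–80.4% power, which is 80% up to rounding.

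**Size of the discrepancy.** Printed minus unrounded downward solution is 0.003–0.010 at 0.25 and 0.005–0.015 at 0.125. In relative terms that is about 7–12% (0.051/0.0478 to 0.093/0.0830) and 13–25% (0.040/0.0354 to 0.075/0.0599). Comparing the unrounded upward and downward solutions gives 14–26% at 0.125. As a relative reduction, the cell worked above implies 0.075/0.125 = 60%, when 0.060/0.125 = 48% is enough.

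**The case against.** The strongest reply is that nothing depends on these cells. The error is conservative: for every affected entry, a true reduction of the printed size has more than 80% power. The sample sizes were set at about 150 children per six-month age interval; Table 3 describes what those sizes can detect and does not generate them. The article commits to no single control proportion, target difference or design effect from the table. The absolute errors, at most 0.015, are smaller than the 0.018–0.028 change from design effect 1.0 to 2.0 within an affected row. All of this stands and limits the consequence.

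It can also be said that the test is two-sided and the entries unsigned, so they are valid as the larger of the two detectable differences. Sidedness, however, sets the critical value and not the alternative. The table claims 80% power, and for a reduction that is not what the entries give.

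Finally, the Outcomes section reports the proportion in each traffic-light category, including green, for which benefit is an increase. With green as the tabulated proportion the entries would be right. But the Sample size section names yellow or red as the main statistic, so that reading is not available.

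**Conclusion.** The point holds. Six of the nine rows of Table 3, 18 of 27 entries, are solved for an increase in the yellow-or-red proportion. For the reduction the trial hypothesises, they overstate the detectable difference by about 7–12% at a control proportion of 0.25 and 13–25% at 0.125; the power at the printed values is 85–89% and 89–95%. The three rows at 0.50 are correct.

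The error understates the trial's ability to show benefit. It does not leave the trial underpowered and calls for no more children. The result rests on equal group sizes, a design effect that multiplies the variance as the footnote says, and the normal-approximation formula that reproduces the printed table exactly. It takes the article's design effects as given and does not test whether they are realistic.

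**What to change.** Recompute the six rows at 0.25 and 0.125 with the exposed proportion equal to the control proportion minus the difference, using the values in the fourth column of the table above. State in the heading of Table 3 that the entries are reductions in the proportion yellow or red. The rows at 0.50 stay as printed.

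If the authors prefer to keep the present figures, the least that is needed is a note that they were solved for an increase and are conservative for a reduction. Restating the rows is better, because the table then answers the trial's own hypothesis.

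The cost is one restated table. Sample size, allocation, conduct and analysis do not change.

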## Discussion

We have presented an evaluation design to estimate the effect of a nurturing care intervention on ECD. Most common designs in evaluation are not applicable to estimating effects on ECD given the nature of the outcome. Scales used to assess dimensions of ECD depend on the specific age of subjects; comparing scores across time is problematic since the way in which ECD is measured varies with age. On the other hand, multiple sources of bias should be considered when selecting a design. The main sources of bias are due to confounding factors such as cohort effects, community effects, self-selection, aging effects, and period effects. Community effects can be controlled by randomization. This type of design is known as a cluster randomized trial [40], where the unit that receives the intervention is an aggregate unit, typically subjects are nested into community clusters. Another advantage of the cluster randomized trial design is related to potential spillover effects. For example, in an educational intervention, subjects that receive the intervention may communicate what they learn to neighbors.

Special consideration should be given to the number of communities to be randomized so that intervention effects may be properly separated from community effects. In the extreme case of just two clusters, even with a random allocation, effects from the intervention are totally confounded with the specific characteristics of the two communities. One of the communities may have better outcomes simply because of its own characteristics and not necessarily because of the applied intervention. It has been suggested a total of between ten and fifteen communities per arm [40] to better separate community effects from intervention effects. In the present study, we specified a total of twenty communities per arm.

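### Table 3 uses one design effect for 750, 900 and 1200 children in the same twenty communities, so its rows fit no single ICC and overstate the precision gained from the larger samples

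*Protocol article*

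**What the plan says.** The Sample size section plans about 150 children per 6-month age interval. That gives 750 per group for A vs D: "these children will be 31–60 months old at their final measurement and compared to children with the same ages in group D". It then lists "ECD outcomes from group B vs group D (*n* = 900) and group C vs group D (*n* = 1200) at the final study calendar period". Table 3 gives detectable differences "given different levels of proportions in the unexposed group (group D"), for "different design effects (DEFF) that consider that measurements in the same community are correlated (DEFF = 1.5, 2.0"), with "a significance level of 0.05 under a bilateral test, and a statistical power of 80.0" per cent. A column with DEFF 1.0 is also shown. The footnote defines the design effect as variance inflation, here from clustering within communities. The article gives no ICC and does not say which cluster size the design effects refer to.

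The number of communities is fixed. Design and setting allocates 80 communities to four groups through twenty blocks of four, and the Discussion confirms it: "In the present study, we specified a total of twenty communities per arm".

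**The concern.** The larger samples come from including more age bands (750/150 = 5, 900/150 = 6, 1200/150 = 8) in the same number of communities. They do not come from more communities. Extra children in communities already sampled add less information than the same number spread over new communities, and the design effect has to show this by rising with cluster size. Holding it constant down a column treats the extra children as if they carried no additional clustering penalty.

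What is at stake is the printed power statement for the shorter-exposure comparisons. C vs D estimates the 12-month effect, one end of the exposure gradient that Design and setting says the trial should detect.

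**Working it through.** **Inputs.** Two-sided 5% level, 80% power, n = 750/900/1200, control proportions 0.50/0.25/0.125 and DEFF 1.5/2.0 (Sample size section and Table 3); twenty communities per group (Discussion). Equal community sizes and no attrition are assumed.

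**Step 1: reproduce Table 3.** With effective size n_e = n/DEFF, control proportion p, exposed proportion q and their mean p̄, solve for d = |q − p| in

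power = Φ{[d − 1.96·√(2p̄(1−p̄)/n_e)] / √([p(1−p)+q(1−q)]/n_e)} = 0.80.

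With q = p + d, all 27 cells agree to about 0.0005. Example: p = 0.50, n = 1200, DEFF 2.0 gives n_e = 600 and d = 0.0805 (stated 0.081). With q = p − d the 0.25 and 0.125 rows do not reproduce, so the table was computed for an increase in the adverse proportion. The 0.50 rows are the same in both directions.

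**Step 2: ICC implied by each row.** Mean cluster size m = n/20 and ICC = (DEFF − 1)/(m − 1).

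| n | m | ICC if DEFF 1.5 | ICC if DEFF 2.0 |
|---|---|---|---|
| 750 | 37.5 | 0.5/36.5 = 0.0137 | 1/36.5 = 0.0274 |
| 900 | 45 | 0.5/44 = 0.0114 | 1/44 = 0.0227 |
| 1200 | 60 | 0.5/59 = 0.0085 | 1/59 = 0.0169 |

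A constant design effect requires the ICC to fall by about 38% from the first row to the last (1 − 36.5/59).

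**Step 3: precision gained from 750 to 1200 at constant ICC** (control 0.50, DEFF 2.0 column). Stated gain: 0.102 − 0.081 = 0.021.

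- 750 row taken as correct: 0.1016 − 0.0920 = 0.0096.
- 900 row taken as correct: 0.0972 − 0.0871 = 0.0101.
- 1200 row taken as correct: 0.0915 − 0.0805 = 0.0110.

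The gain is roughly half the stated one under every anchor.

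**Step 4: anchor on A vs D (an assumption).** DEFF = 1 + (m − 1)·ICC gives 1 + 44·0.0137 = 1.60 and 1 + 44·0.0274 = 2.21 for B vs D, and 1 + 59·0.0137 = 1.81 and 1 + 59·0.0274 = 2.62 for C vs D. At control 0.50:

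| Comparison | Column | Stated | At constant ICC | Power at stated |
|---|---|---|---|---|
| B vs D | 1.5 | 0.081 | 0.083 | 78% |
| B vs D | 2.0 | 0.093 | 0.098 | 76% |
| C vs D | 1.5 | 0.070 | 0.077 | about 73% |
| C vs D | 2.0 | 0.081 | 0.092 | 69% |

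Check of the last line: n_e = 1200/2.616 = 458.6, p̄ = 0.5405, so (0.081 − 1.96·0.0329)/0.0328 = 0.50 and Φ(0.50) = 0.69.

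**Step 5: anchor on the 1200 row instead.** The C vs D cells are then right. At control 0.50, A vs D needs 0.082/0.092 (stated 0.088/0.102) and B vs D needs 0.077/0.087 (stated 0.081/0.093), so those stated cells are pessimistic.

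**Step 6: the hypothesised direction.** The hypothesis is better development, that is, a lower proportion in the yellow or red category. Solving with q = p − d on the A vs D anchor:

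| Control | Comparison | Needed (1.5/2.0) | Stated (1.5/2.0) |
|---|---|---|---|
| 0.25 | B vs D | 0.069/0.080 | 0.073/0.085 |
| 0.25 | C vs D | 0.064/0.076 | 0.063/0.073 |
| 0.125 | B vs D | 0.050/0.058 | 0.058/0.068 |
| 0.125 | C vs D | 0.047/0.055 | 0.050/0.058 |

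Only C vs D at 0.25 falls short here, and only slightly. The 0.50 results of Step 4 are unchanged.

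**The case against.** A reader might infer that the stated differences for B vs D and C vs D are too optimistic throughout, or that the trial is underpowered. The documents do not support that. With no ICC and no reference cluster size given, optimism appears only if the design effects are tied to a row below 1200, and under the 1200-row anchor it disappears (Step 5). Tying them to A vs D is a natural reading, because the article sets out that comparison first and calls the others possible, but it is still an assumption. Even on that anchor, six of the eight cells in Step 6 stay conservative for a reduction.

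It can also be said that Table 3 is a sensitivity grid, that the sample size came from 150 children per age interval and was not solved from a design effect, and that the analysis adjusts standard errors for clustering anyway. All of this is true and limits the consequences. In the DEFF 1.5 scenario the corrected values (1.60, 1.81) also lie within the tabulated range. Only the 2.0 scenario leaves it (2.21, 2.62).

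Finally, the ICC might really be lower in a wider age band. The article does not say so, and group D is the same twenty communities in every comparison.

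What survives all of this is the inconsistency between rows and the overstated gain. The conservative direction of the calculation partly hides the problem in some cells, but it is a separate feature of the table and does not justify a constant design effect.

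**Conclusion.** The point holds as an internal inconsistency in Table 3. No single ICC fits the three rows of either clustered column, and the precision gained from 750 to 1200 children is overstated under any anchor (0.021 stated against about 0.010 to 0.011 at control 0.50, DEFF 2.0).

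A shortfall in power is conditional. On the A vs D anchor it matters mainly for C vs D at control 0.50, where power is about 73%/69% against the stated 80%. For B vs D the change is at most 0.005 (power at 0.50 of 76% to 78%). For a reduction, the shortfall is confined to the 0.50 rows and, slightly, C vs D at 0.25. A vs D is unaffected on this anchor.

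These figures assume an exchangeable within-community correlation, equal community sizes and no attrition.

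**What to change.** State an ICC, or a short range labelled as assumed, together with the mean cluster size for each comparison. Compute DEFF = 1 + (n/20 − 1)·ICC in each row, with an allowance for unequal community size: eligibility sets only a lower limit on the number of under-fives and population size is a stratifier, so sizes will vary. Compute the differences as reductions, the hypothesised direction, and restate Table 3 with ICC columns in place of fixed-DEFF columns.

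Data in hand may inform the ICC: "Baseline measurements were obtained for a total of 1176 children", according to Trial status, and these appear to be group A's baseline. Two caveats belong beside any such estimate. Group A children were 1 to 30 months old, whereas A vs D is analysed at 31 to 60 months with different age-specific items. The total also includes 412 children whose caregivers declined the programme, while the randomised comparison rests on enrolling families.

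The cost is one recalculated table and a sentence of justification. Enrolment, allocation and analysis stay as they are. Some stated figures, mainly for C vs D, may become less favourable.
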